#### Sample size calculations

The anticipated absolute continuous abstinence rate for group A (weeks 9 to 12) for the primary outcome measure is set at 45%. This is based on the quit rates reported for combination NRT (nicotine patch and short-acting NRT) [16]. Trials of combination NRT were used to inform this estimate because: (1) randomized trials of a high-dose nicotine patch are not available to inform the projected treatment size, and (2) similar to nicotine patch, combination NRT also allows upward titration to reach satiety. It is anticipated that the abstinence rates for an active titrated nicotine patch will at least meet, if not exceed those of combination NRT. The estimated continuous abstinence rates during weeks 9 to 12 for group B are 30% based on published literature of the effects of a standard nicotine patch in clinical trials [41]. Assuming *p* = .05, a sample of 163 per group provides 80% power to detect this difference at weeks 9 through 12. With an estimated 20% quit rate during the 2-week run-in period, we therefore plan to recruit approximately 500 participants into the trial until we have 400 eligible for randomization. Randomized groups of 200 participants per group will ensure that the group is adequately powered for longer-term outcomes as well. Since we are using ITT, all participants randomized to a treatment arm will be included in the analysis so our *n* will remain constant and our power to detect a difference between groups should not be significantly affected by loss to follow-up as long as it is more or less equal in the two arms. Our overall proportion of participants defined as quit will decrease but the difference between the two groups should remain the same.

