### Randomization

After the 2-week run-in phase, stage 2 will be initiated, in which participants who fail to achieve 7-day abstinence (self-report of not smoking for at least the past 7 days at week 3 study visit) will be randomly assigned to the experimental (group A, escalating active patches) or a control condition (group B, escalating placebo patches) for 10 additional weeks of treatment. To maintain allocation concealment, participants will be randomized 1:1 in permuted blocks of varying sizes. The randomization schedule will be generated by the research pharmacist under guidance of the co-investigator statistician and stored securely in the pharmacy. Only the research pharmacists will be unblinded to group assignment. Participants, investigators, and research staff will be blind to group A or B assignment. Participants who stop smoking during the run-in phase will not be randomized but instead will continue with an open-label nicotine patch 21 mg/day (group C) for another 10 weeks. We estimate that 20% of participants will be able to quit smoking in the first 2 weeks to comprise group C. This group will be used to test some of the exploratory hypotheses outlined above.

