#### Secondary outcome measures

The secondary outcome measures are self-reported continuous abstinence through week 9 to weeks 26 and 52, confirmed by urinary cotinine < 200 ng/ml (assay limit of detection) at the 26- and 52-week follow-up visits.

To test the hypothesis that rates of nicotine metabolism moderate the effect of patch titration, we will compare the quit outcomes in rapid versus slow nicotine metabolizers within and among the treatment groups.

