### Statistical analysis

Descriptive statistics will be used to summarize baseline characteristics. Baseline characteristics will be examined for any statistically significant differences between randomized groups. Such variables will be used as covariates in an adjusted analysis. The primary analysis will follow the intention-to-treat principle (ITT) [40] whereby all participants that drop out of the study or are otherwise lost-to-follow-up will be classified as still smoking. The primary analysis will compare the proportions of patients in each group (group A vs group B) to achieve smoking cessation using Pearson’s chi-square test. Additional analysis will employ logistic regression to adjust for variables known to be strongly associated with smoking cessation, including but not limited to age, sex, and psychiatric comorbidities.

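### The statement that 200 per group ensures adequate power at weeks 26 and 52 rests on long-term assumptions that the protocol does not state

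*Protocol article*

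**What the plan says.** All of the sizing is in the Sample size calculations section of the Protocol article.

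- Group A: "The anticipated absolute continuous abstinence rate for group A (weeks 9 to 12) for the primary outcome measure is set at 45" per cent.
- Group B: "The estimated continuous abstinence rates during weeks 9 to 12 for group B are 30" per cent.
- Power: "a sample of 163 per group provides 80% power to detect this difference at weeks 9 through 12", at a significance level of 0.05.
- Long-term outcomes: "Randomized groups of 200 participants per group will ensure that the group is adequately powered for longer-term outcomes as well". No week-26 or week-52 rate, difference or power value accompanies this.

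The same paragraph then argues that power should survive loss to follow-up. Everyone randomized stays in the denominator and, provided loss is about equal in the two arms, the overall quit proportion drops while the between-group difference is expected not to change.

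Under Secondary outcome measures, the long-term endpoints are "self-reported continuous abstinence through week 9 to weeks 26 and 52", confirmed by urinary cotinine. Under Statistical analysis, participants who drop out are classed as smoking in the primary analysis. The week-26 and week-52 comparisons are planned as logistic regression with inverse-probability weights (Analysis of secondary and tertiary outcomes).

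**The concern.** The article presents adequate long-term power as a property of the design, but the only rates behind it belong to an earlier and easier endpoint. A participant who is continuously abstinent from week 9 to week 26 or 52 must also have been abstinent in weeks 9–12. Long-term quitters are therefore a subset of the weeks 9–12 quitters, and the rate in each arm can only stay level or fall.

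The one supporting argument in the paragraph, that equal loss leaves the difference unchanged, does not hold when equal proportions are lost and counted as smoking. Both rates are then multiplied by the same factor, and so is the difference.

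What is at stake is interpretation. If a non-significant week-26 or week-52 result comes from a trial described as assured of adequate power, it invites the reading that the benefit did not last. Whether that reading is fair depends on long-term rates that the article does not give.

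**Working it through.** **Inputs.** From Sample size calculations: 45% vs 30% in weeks 9–12, significance level 0.05, 163 per group for 80% power, 200 per group planned. From Randomization: "participants will be randomized 1:1 in permuted blocks of varying sizes". From Statistical analysis: groups compared on the proportion "to achieve smoking cessation using Pearson’s chi-square test". Sidedness is not stated. Two-sided is used because it reproduces the article's figure and one-sided does not. Relapse after week 12 is not given, so every long-term rate below is an assumption.

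**Step 1: reproduce the stated sample size.** With p̄ = (0.45 + 0.30)/2 = 0.375 and the pooled-variance formula without continuity correction:

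n = [1.96 × √(2 × 0.375 × 0.625) + 0.8416 × √(0.45 × 0.55 + 0.30 × 0.70)]² / 0.15²

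= [1.96 × 0.6847 + 0.8416 × 0.6764]² / 0.0225 = 162.3, rounded up to **163**.

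This matches the article. A one-sided test would need 128. Power at 163 per group is 80.2%.

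**Step 2: power at 200 per group for the primary outcome.** Power = Φ{[(pA − pB)√n − 1.96√(2p̄(1 − p̄))] / √(pA(1 − pA) + pB(1 − pB))}. For 45% vs 30% and n = 200:

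Φ{[0.15 × 14.142 − 1.96 × 0.6847] / 0.6764} = Φ(1.15) = **87.5%**.

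**Step 3: equal proportional relapse in both arms.** Set pA = 0.45(1 − r) and pB = 0.30(1 − r), so that the risk ratio stays at 1.5. The difference is 15 × (1 − r) points.

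| r | A vs B | Difference (points) | Power at 200 per arm | n per arm for 80% |
|---|---|---|---|---|
| 0% | 45.0% vs 30.0% | 15.0 | 87.5% | 163 |
| 12% | 39.6% vs 26.4% | 13.2 | 80.4% | 199 |
| 13% | 39.2% vs 26.1% | 13.1 | 79.7% | 202 |
| 20% | 36.0% vs 24.0% | 12.0 | 74.7% | 228 |
| 30% | 31.5% vs 21.0% | 10.5 | 66.6% | 275 |
| 50% | 22.5% vs 15.0% | 7.5 | 48.5% | 424 |

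The 80% line is crossed at r = 12.6%. Exact binomial power of the Pearson test agrees: 80.2% at r = 12.5% and 79.8% at r = 13%. The crossing is at 12.8% with the arcsine formula, 13.4% with unpooled variance and about 8% with a continuity correction.

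**Step 4: constant odds ratio.** The odds ratio implied by 45% vs 30% is (0.45/0.55)/(0.30/0.70) = 1.91. Holding it fixed:

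| A vs B | Power at 200 per arm |
|---|---|
| 38.9% vs 25% | 85% |
| 32.3% vs 20% | 80% |
| 25.2% vs 15% | 72% |
| 17.5% vs 10% | 59% |

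Here 80% is reached when about a third of group B quitters have relapsed (20/30) and about 28% of group A quitters have (32.3/45).

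**Step 5: constant 15-point difference.** Power rises: 92.2% at 35% vs 20% and 97.9% at 25% vs 10%. The loss needed is unequal, though. To reach 25% vs 10%, group A loses 1 − 25/45 = 44% of its quitters and group B loses 1 − 10/30 = 67%. That is not equal proportional loss.

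**Step 6: smallest detectable group A rate at 200 per arm, 80% power.** It is 20.0% against 10% (10 points) and 26.3% against 15% (about 11 points).

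**The case against.** The strongest reply is that the 12–13% threshold is not a property of the plan. It needs the same proportion of quitters to relapse in both arms, and the article assumes nothing about relapse. Its equal-loss condition concerns loss to follow-up. Other patterns move the answer widely. A constant odds ratio, the natural scale for the planned logistic regression, keeps power at or above 80% until about 32% vs 20%. Relapse of 20% in A and 30% in B gives 92%, while 30% in A and 20% in B gives 39%. This stands, and the threshold should always be quoted with its assumption.

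Three further points also stand:

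- No stated figure is wrong, since 163 per group reproduces exactly.
- The outcomes are secondary, need not be powered and may still be tested.
- The long-term rates may be in the full protocol, which is not shown. Their absence from a condensed article is not by itself a fault. The fault is a guarantee that the article's own figures and argument do not deliver.

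A reader might infer that the trial is underpowered at 26 and 52 weeks, or that its power there is no better than even. The article gives no long-term rate from which that could follow, and power near 48% needs r of about 50% under the fixed ratio. A reader might also infer that counting missing participants as smokers lowers power below the values tabulated. That is not established. The article ties that rule to the primary analysis and plans a weighted regression for the long-term outcomes. Where the rule does apply, such losses are already part of r.

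**Conclusion.** The assurance of adequate long-term power does not follow from what the article states. It depends on long-term rates and a relapse pattern that are not given, and its supporting premise of an unchanged difference fails when equal proportions are lost and counted as smoking.

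The size of the shortfall depends on the assumption made. The 37 extra participants per arm (200 − 163) cover about 12.6% relapse if the risk ratio stays at 1.5. They cover relapse of roughly a third in group B if the odds ratio stays at 1.91, and any fall in the rates if the 15-point difference somehow persists. All figures refer to an unweighted two-sided 5% comparison. Power for the planned weighted regression cannot be computed from the article. The sample size for the primary outcome stands.

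**What to change.** In Sample size calculations:

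1. Replace the assurance about longer-term outcomes with the assumed week-26 and week-52 rates in each arm and the resulting power at 200 per group. Alternatively, give the smallest difference detectable with 80% power, which is about 10–11 points at a control rate of 10–15%.
2. Correct the closing sentence on loss to follow-up. It should say that loss in equal proportions, counted as smoking, reduces the absolute difference and the power.

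The cost is a few sentences and a less favourable stated property. No participants are added, and the design, the primary analysis and the primary-outcome sample size stay as they are.

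### Counting dropouts as smokers shrinks the A–B difference under equal loss, so the protocol is wrong that the difference and the power are preserved

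*Protocol article*

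**What the plan says.** All references are to the protocol article. Under Statistical analysis, the primary analysis is a Pearson chi-square comparison of groups A and B by intention to treat, in which "all participants that drop out of the study or are otherwise lost-to-follow-up will be classified as still smoking".

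Under Sample size calculations, the assumed continuous abstinence rates for weeks 9 to 12 are 45% in group A and 30% in group B, and "a sample of 163 per group provides 80% power to detect this difference at weeks 9 through 12". The plan is to randomize 400, for this reason: "Randomized groups of 200 participants per group will ensure that the group is adequately powered for longer-term outcomes as well".

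The same section then deals with loss to follow-up. Because everyone randomized is analysed and n stays constant, it holds that "our power to detect a difference between groups should not be significantly affected by loss to follow-up", provided that loss is about equal in the arms. It closes with: "Our overall proportion of participants defined as quit will decrease but the difference between the two groups should remain the same". No dropout rate and no allowance for dropout are given.

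**The concern.** The argument treats a constant denominator as if it protected power. Power also depends on the size of the difference. When missing is scored as smoking, each lost participant who would have quit moves from success to failure. Group A is expected to have more such people than group B, so the same percentage loss removes more successes from A than from B. Equal loss preserves the ratio of the two rates, not their difference.

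What is at stake is a stated robustness property of the primary sample size. A reader of a null result who relied on it could believe that dropout had left the power untouched, when the difference the trial could observe had been diluted by the scoring rule.

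**Working it through.** **Inputs from the protocol article.** Rates 0.45 and 0.30, alpha 0.05, 163 per group for 80% power, 200 per group planned (Sample size calculations); 1:1 allocation (Randomization); Pearson chi-square, dropouts scored as smoking (Statistical analysis). Sidedness is not stated; two-sided reproduces the stated n, while one-sided gives 128.

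**Assumed, because the article does not say.** The dropout fraction d (range 0 to 30%); that 45% and 30% are rates before loss; and how often dropouts would have quit.

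**Step 1: reproduce the stated figure.** Pooled null variance, no continuity correction, mean rate (0.45 + 0.30)/2 = 0.375:

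n = [1.96 × √(2 × 0.375 × 0.625) + 0.8416 × √(0.45 × 0.55 + 0.30 × 0.70)]² / 0.15² = 162.3, rounded up to 163.

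Power at 163 per group is 80.2%. The stated figure is right for the stated rates.

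**Step 2: effect of equal loss unrelated to outcome.** The rates become 0.45(1 − d) and 0.30(1 − d). The difference is 0.45(1 − d) − 0.30(1 − d) = 0.15(1 − d).

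**Step 3: power at 200 per arm.** With p_A and p_B the diluted rates and p̄ their mean:

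power = Φ{ [(p_A − p_B) − 1.96 × √(2p̄(1 − p̄)/200)] / √(p_A(1 − p_A)/200 + p_B(1 − p_B)/200) }

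For d = 20%: p_A = 0.36, p_B = 0.24, p̄ = 0.30; (0.12 − 1.96 × 0.0458)/0.0454 = 0.664, and Φ(0.664) = 74.7%.

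| Loss d in each arm | Rates A vs B | Difference (points) | Power, 200 per arm |
|---|---|---|---|
| 0% | 45.0% vs 30.0% | 15.0 | 87.5% |
| 5% | 42.75% vs 28.5% | 14.25 | 84.8% |
| 10% | 40.5% vs 27.0% | 13.5 | 81.7% |
| 15% | 38.25% vs 25.5% | 12.75 | 78.3% |
| 20% | 36.0% vs 24.0% | 12.0 | 74.7% |
| 30% | 31.5% vs 21.0% | 10.5 | 66.6% |

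Power crosses 80% at d = 12.6%. Other uncorrected approximations give 12.8% (arcsine) and 13.4% (unpooled).

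**Step 4: dropouts who are less likely to quit.** Let dropouts have quit at a fraction r of their arm's overall rate. Both rates are then multiplied by (1 − d·r), and the difference is 15(1 − d·r) points. The 80% crossing is where d·r = 12.6%, so d = 12.6%/r.

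| r | Loss at which power reaches 80% | Power at 20% loss |
|---|---|---|
| 1 | 12.6% | 74.7% |
| 0.75 | 16.8% | 78.3% |
| 0.5 | 25.2% | 81.7% |
| 0.25 | about 50% | 84.8% |

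**Step 5: when would the protocol's sentence be true?** The quit proportion falls and the difference stays at 15 points only if each arm loses the same absolute share k of would-be quitters. The loss among quitters is then k/0.45 in A and k/0.30 in B, which is 0.45/0.30 = 1.5 times as high in B. For k = 5 points that is 11.1% in A and 16.7% in B. This is not equal loss, and the article gives no reason to expect it.

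**The case against.** The strongest reply is that the size of the effect rests on two things the article does not settle.

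First, dropouts from cessation treatment may be mostly people who would not have quit. The scoring rule reflects that view, and Step 4 shows that dilution is milder to the extent that it is true. Second, 45% and 30% are taken from cited literature. If those rates already count dropouts as smokers, multiplying by (1 − d) counts the loss twice, and the planned power stays at 87.5%.

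Both points stand as limits on the magnitude. Neither rescues the sentence. If only would-be smokers dropped out, or if the rates already included the loss, the quit proportion would not fall, yet the article says that it will.

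A reader might infer three stronger things, which the documents do not support:

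- *That 80% power is lost at 12–13% dropout as a fixed property of the design.* That threshold needs r = 1 and rates before loss; at r = 0.5 it is about 25%.
- *That the stated 80% power is wrong, or that the trial as planned is underpowered.* The 163 per group is correct at the stated rates, and the trial randomizes 200. The extra 37 per arm are justified by longer-term outcomes, but in effect they absorb moderate loss for the primary outcome. Power at 163 per arm after loss (73.4% at 10%) describes a trial that is not planned.
- *That the protocol expects poor retention.* The Discussion says only that trial burden could hamper retention in participants with psychiatric or substance use comorbidities, and it gives no rate.

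Nor does a falling overall proportion by itself force the difference down. Step 5 gives the exception, so the conclusion needs loss that is proportional among quitters.

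**Conclusion.** The point holds as an error of reasoning in the justification of the primary sample size. With dropouts scored as smokers and loss equal in the arms, the A–B difference does not stay the same; it is 15(1 − d·r) points. At r = 1 the miss rate roughly doubles at 20% loss, from 12.5% to 25.3%, which is hard to call insignificant. At r = 0.5 and the same loss, power is still 81.7%.

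The direction is certain once any would-be quitters are lost in equal proportion. The size is conditional on d, on r and on what the 45% and 30% represent, and the article fixes none of them. The randomized number, endpoint, test and scoring rule are not called into question.

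**What to change.** In Sample size calculations:

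1. Keep the statement that all randomized participants are analysed.
2. Remove the claims that the difference is unchanged and that power is not materially affected by equal loss.
3. State that scoring missing as smoking dilutes the expected difference to 15(1 − d·r) points.
4. Say whether 45% and 30% already count dropouts as smokers. If they do, say so and do not dilute them again.
5. Otherwise, report power for 200 per arm over a range of d and r, for example 82%, 75% and 67% at 10%, 20% and 30% loss with r = 1, and quote the value at the expected loss as the trial's power.

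This is a change of wording, and it needs no extra patients. The cost is a less favourable stated power.

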### Ethics and dissemination

The study has been approved by the hospital Research Ethics Boards (REB) at both study sites. Protocol amendments are submitted to each hospital REB for approval prior to implementation. Once approved, the amendment is submitted to Health Canada in compliance with procedures for regulated trials. If the protocol change necessitates revisions to the consent form, all participants currently enrolled in the study will be told of the changes and asked to sign the new version of the consent form. All REB-approved documents are version controlled and stored in the investigator study binder (ISB) with a corresponding log of amendments.

Trained study staff (research analyst) will conduct the informed consent procedure and obtain written informed consent as per Good Clinical Practice guidelines prior to initiating any other study-related activities. The research analyst will provide the participant with the study consent form (Additional file 2) to read carefully, or have it read to them if applicable. Once the participant has read through the consent form, the study staff will prompt the participant for any questions, concerns, or comments. Participants that consent to the main study will be given the opportunity to participate in the Genetics sub-study (separate consent form; Additional file 3). Participants may elect to take part in the Genetics sub-study at any point during their participation in the main study. Participation in the sub-study includes collecting one venous blood sample (10 ml). The blood sample will be labeled with a UPC code and no other identifying information stored in a locked freezer. Genotype analyses of nicotine metabolizing enzymes and other genes related to smoking cessation treatment outcomes will be conducted.

All personal health information collected for study purposes will be stored securely as per Good Clinical Practice guidelines. Original copies of the Informed Consent documentation will be stored in a locked filing cabinet behind two locked doors. This documentation will be kept separate from all other study-related documents. Only the sponsor (CAMH) will have full access to the final trial dataset. All data and results from the subsite (UOHI), excluding PHI, are owned by CAMH.

#### Dissemination

At the completion of the study, the PI will share the results through academic presentations and publication in peer-reviewed journals. Findings will be incorporated into Canadian clinical smoking cessation practice guidelines. In addition, results will be available to view on clinicaltrials.gov.

## Discussion

Fixed doses of NRT can be ineffective for many patients as the given dose can exceed some individuals’ level of tolerance to nicotine while for others it may be an inadequate dose that fails to sufficiently quell withdrawal and cravings [23]. By personalizing doses of NRT, clinicians may be able to assist individuals on either end of the dosing spectrum. The aim of this study is to understand the efficacy of 10 weeks of personalized dosing of a nicotine patch in motivated smokers unable to quit after 2 weeks of a standard nicotine patch (21 mg). The study optimizes the current evidence-based practice for smoking cessation treatment (NRT with brief behavioral counseling) using a personalized dosing approach. Given the pragmatic nature of the study and the heterogeneity of the participants, the results from this study will be externally valid and will be applicable to a wide variety of healthcare settings.

The challenges encountered to date with the implementation of this investigator-initiated study have been primarily related to the lack of ready access to matching placebo patches that satisfy the safety and manufacturing requirements of clinical trial regulators in Canada. In addition, although the design is pragmatic to include those with psychiatric or substance use comorbidities, trial burden (weekly visits, adherence to the protocol) might make retention problematic for these participants. Concurrent cannabis smoking and alcohol consumption could affect the primary outcome and the outcome measure had to be chosen to limit false positives.

Given the strong link between smoking, cancer, and cardiovascular disease and evidence that quitting smoking at any age diminishes this risk, even small increases in absolute quit rates can have a substantial population-level impact on reducing the incidence of smoking-related disease, mortality rates, and associated healthcare costs.

